## Abstract

**Background:**

Epilepsy is a neurological disorder, characterized by recurrent unprovoked seizures which have a high impact on the individual as well as on society as a whole. In addition to the economic burden, epilepsy imposes a substantial burden on the patients and their surroundings. Patients with uncontrolled epilepsy depend heavily on informal care and on health care professionals. About 30% of patients suffer from drug-resistant epilepsy. The ketogenic diet can be a treatment of last resort, especially for children. The beneficial effect of the ketogenic diet has been proven, but information is lacking about its cost-effectiveness. In the current study we will evaluate the (cost-) effectiveness of the ketogenic diet in children and adolescents with intractable epilepsy.

**Methods/Design:**

In a RCT we will compare the ketogenic diet with usual care. Embedded in this RCT will be a trial-based and model-based economic evaluation, looking from a societal perspective at the cost-effectiveness and cost-utility of the ketogenic diet versus usual care. Fifty children and adolescents (aged 1-18) with intractable epilepsy will be screened for eligibility before randomization into the intervention or the usual care group. The primary outcome measure is the proportion of children with a 50% or more reduction in seizure frequency. Secondary outcomes include seizure severity, side effects/complaints, neurocognitive, socio-emotional functioning, and quality of life. Costs and productivity losses will be assessed continuously by a prospective diary and a retrospective questionnaire. Measurements will take place during consults at baseline, at 6 weeks and at 4 months after the baseline period, and 3, 6, 9 and 12 months follow-up after the 4 months consult.

**Discussion:**

The proposed research project will be the first study to provide data about the cost-effectiveness of the ketogenic diet for children and adolescents with intractable epilepsy, in comparison with usual care. It is anticipated that positive results in (cost-) effectiveness of the proposed intervention will contribute to the improvement of treatment for epilepsy in children and adolescents and will lead to a smaller burden to society.

**Trial registration:**

The study has been registered with the Netherlands Trial Registry (NTR2498).

## Background

Epilepsy is a brain disorder characterized predominantly by recurrent and unpredictable interruptions of normal brain function. Seizures are transient occurrences of signs and/or symptoms due to such abnormal excessive or synchronous neuronal activities in the brain [1]. Different parts of the brain can be the site of such discharges. The clinical manifestations of seizures will therefore vary and depend on where in the brain the disturbance first starts and how far it spreads. Transient symptoms can occur, such as loss of awareness or consciousness and disturbances of movement, sensation, mood or mental function [1]. Furthermore, epilepsy is a major cost-intensive and worldwide health problem [2]. In 2000, the aggregate burden due to epilepsy was 0.5% of the total burden of diseases in the world [3]. In Europe, about 3.4 million people suffer from epilepsy [4]. The annual total costs of epilepsy in Europe are €15.5 billion [5]. In the Netherlands, direct medical costs were €221 million in 2005 [6]. In addition to the economic burden, epilepsy imposes a substantial burden on the patients themselves and their surroundings.

In the Netherlands, the point prevalence of epilepsy in children and adolescents between 0-18 years is 4.77 boys, and 4.55 girls per 1,000 persons. The yearly incidence of epilepsy in the Netherlands for children and adolescents between 0-18 years is 0.58 per 1,000 boys and 0.53 per 1,000 girls [7]. Although epilepsy is treatable with anti-epileptic drugs in the majority of cases, about 30% of patients suffer from drug-resistant epilepsy [8]. Patients with uncontrolled epilepsy heavily depend on informal care (family and friends) and on health care professionals (neurologists, social workers, psychologists etc.). Complications due to intractable epilepsy result in frequent hospitalizations and many of these patients are institutionalized. Patients with drug-resistant epilepsy can potentially benefit from a ketogenic diet. The ketogenic diet is a high-fat, low carbohydrate, normocaloric diet that mimics the metabolic state of fasting. During a prolonged fast, body energy requirements are met by lipolysis and ß-oxidation of fatty acids rather than by the breakdown of carbohydrates. The ketogenic diet maintains an anabolic nutritional state in a metabolic situation of fasting. Ketone bodies may produce an anticonvulsant effect, presumably due to changes in cerebral energy metabolism, in cell properties decreasing excitability, in neurotransmitter function, in circulating factors acting as neuromodulators and in the brain's extracellular milieu [9]. The ketogenic diet is generally used for a period of up to 3 years. Seizure control benefits are typically seen within 1-3 months of starting the diet. The international study group reports that the diet should be utilized for at least 3 1/2 months before deciding to discontinue it [10]. The diet can be discontinued earlier if seizures worsen beyond expectations or if adverse effects cannot be corrected [11]. Medications are tapered once the efficacy of the diet has been established (usually within 3-6 months of diet initiation). The diet is gradually tapered off by lowering its fat content and increasing the carbohydrate and protein portion of the diet until ketosis is eliminated. Tapering starts after 2 years of treatment, or earlier in case of intolerable side effects, or in case of ineffectiveness.

Currently the scientific and clinical attention paid to the role of the ketogenic diet is negligible. This means that a ketogenic diet is often overlooked and underutilized as a treatment option for children with intractable epilepsy. An important reason for this is that relatively few children and their parents can comply with the stringent diet. Therefore, physicians are often reluctant to initiate the diet. To offer more children the opportunity to benefit from a ketogenic diet, we suggest that the diet should be initiated and monitored under strictly controlled circumstances in order to maximize compliance.

The beneficial effect of a ketogenic diet has been studied in multiple observational studies [12-20], reviews [21-24] and in one randomized controlled trial [25]. Nevertheless, there is a lack of information about the cost-effectiveness of the ketogenic diet, and consequently health authorities have not been convinced of its usefulness.

The aims of our prospective study are to provide more evidence about the effectiveness and to investigate the cost-effectiveness of treatment with a ketogenic diet KD in comparison with usual care in children and adolescents with drug-resistant epilepsy who are not eligible for epilepsy surgery.

## Methods/Design

The design and methods of a randomized controlled trial (RCT) evaluating the (cost-) effectiveness of a ketogenic diet in comparison with usual care in children and adolescents with intractable epilepsy are described in this paper. This study has been approved by the ethics committee of the Academic Medical Centre Utrecht, the Netherlands.

### Research question

We defined the following research questions:

#### I) Effect evaluation

(1) What are the effects of the ketogenic diet in comparison with usual care with respect to changes in seizure frequency and seizure severity, side effects/complaints, neurocognitive, socio-emotional functioning, and quality of life?

#### II) Economic Evaluation

The economic evaluation will consist of a trial-based and a model-based economic evaluation study.

##### IIa) Trial-based economic evaluation

(1) From a social perspective, is the ketogenic diet, in comparison with usual care, preferable in terms of costs, effects and utilities?

(2) What is the incremental cost-effectiveness ratio (ICER) of the ketogenic diet in comparison with usual care?

##### IIb) Model-based economic evaluation

(1) In comparison with usual care, is the ketogenic diet preferable in terms of costs and utilities during the remaining life expectancy of the study population?

### Design

The proposed study is a prospective RCT. The subjects will be randomized to either the ketogenic diet or to usual care. The trial flow of the proposed subject enrolment and randomization procedures are shown graphically in Figure 1. Embedded in this RCT will be a short-term trial-based economic evaluation and a long-term modelling study to investigate the long-term cost-effectiveness and cost-utility of the ketogenic diet versus usual care.

**Figure 1 F1:**
[figure not shown]
**Flowchart of the study**.

### Participants

The patient population consists of children and adolescents with drug-resistant epilepsy. Patients are eligible to participate if they meet the following criteria: age between 1 and 18 years old; having uncontrolled seizures; not eligible for epilepsy surgery; no fatty acid oxidation disorders and related diseases; no diabetes and hyperinsulinism; no prolonged QT-time syndrome; no hypercholesterolemia or hypertriglyceridemia; no severe liver, kidney or pancreas diseases; no renal tubular acidosis; no severe behavioral disorder; no malnutrition; no treatment with topiramate or acetazolamide and no positive family history or other risk factors for kidney stones or acidosis.

### Recruitment

Potential participants are screened for exclusion criteria by their own attending paediatrician, neurologist or paediatric neurologist. Children who are eligible to be treated with a ketogenic diet are subsequently referred to the multidisciplinary ketogenic diet team at the epilepsy centre Kempenhaeghe in the Netherlands. Eligible children and their parents will first receive information by telephone before getting an invitation for an information visit. During the information visit eligibility is checked by the multidisciplinary team. If they are interested, parents, adolescents and/or children can find information about the study on the website http://www.ketogeenmenu.nl. Parents and potential candidates who are considering participating in the study will have at least one week to decide, before signing informed consent.

### Sample Size

A 50% reduction in seizure frequency is considered clinically relevant and is defined as success. Assuming a minimum detectable difference in success rate of 35% between the ketogenic diet group and usual care, and assuming that alpha = 5% and power = 80%, we need 22 children for each group. Taking dropouts into account, we need 50 children in total. A drop-out is defined as a child who drops out of the study before the first consultation with the neurologist; this is scheduled 6 weeks after initiating the KD or 6 weeks after randomization to usual care.

### Randomization and procedure

Randomization will occur halfway through the 4 week baseline period. We will use a software package (ALEA) to support the online patient registration and randomization which will be based on the minimization method. Patients will be stratified according to age (1-6 years, 7-12 years, 13-18 years), having a PEG/tube or not, and whether the child is living at a residential centre or attends the epilepsy centre as an outpatient while she/he lives at home. In view of the nature of the treatments, blinding of the patients and researchers is not possible.

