#### Primary outcome

##### Seizure frequency

A seizure calendar is used to record seizures. Types of seizures are described and labelled in accordance with ILAE classification. The number and type of seizures are recorded on the dates they occur.

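### Allocation is made midway through the baseline of an unblinded trial, and the article does not keep the post-allocation weeks out of the seizure count that defines response

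*Protocol article*

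**What the plan says.** On timing, the section Randomization and procedure of the protocol article says: "Randomization will occur halfway through the 4 week baseline period". The same section says: "In view of the nature of the treatments, blinding of the patients and researchers is not possible".

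On the outcome, the abstract says: "The primary outcome measure is the proportion of children with a 50% or more reduction in seizure frequency". The Sample Size section agrees: "A 50% reduction in seizure frequency is considered clinically relevant and is defined as success". Under Seizure frequency, the measurement is described so: "A seizure calendar is used to record seizures". That section adds that the number and type of seizures are entered by date of occurrence.

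The four-week period is the only baseline period the article defines. It does not say that the allocation is held back until that period ends, that the reference rate uses only the weeks before randomization, or that anyone blinded to the allocation counts seizures.

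The article also gives two clocks for the 6-week visit. In Sample Size, the usual-care visit is counted from randomization. In the notes to Figure 2 and Table 1, T2 is counted from the end of the baseline period.

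**The concern.** A responder is defined by a ratio: follow-up seizure rate over baseline seizure rate, at or below one half. Randomization makes the arms comparable on what is measured before allocation. Here, part of the denominator may be measured after it, by people who know whether the child is about to be admitted for the diet or will wait four months for it. If that knowledge changes how carefully seizures are noted, the baseline shifts by arm, and so does the true reduction a child needs to count as a success.

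Open-label recording during follow-up is hard to avoid in a trial of this kind. The exposure at baseline is avoidable and comes on top of it. The same question applies to any T0 questionnaire or test completed after allocation, although the article does not date these within the four weeks.

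**Working it through.** **Share of baseline after allocation.** Randomization at 2 of 4 weeks leaves 2/4 = 50% of baseline time after allocation. This is exact for time, not necessarily for the number of seizures.

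**Shift of the cut-off.** Suppose the count in weeks 3-4 is mis-recorded by a fraction b, and true seizure rates are equal in the two halves. Then

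recorded baseline = true baseline × (1 + b/2)

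true reduction needed = 1 − 0.5 × (1 + b/2)

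- b = +10%, +20%, +30%: 47.5%, 45%, 42.5%.
- b = −10%, −20%, −30%: 52.5%, 55%, 57.5%.

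**Effect on response rates with no true effect.** Assume the follow-up/baseline ratio is lognormal with log SD s, and let p be the success rate without mis-recording. The recorded rate is Φ(Φ⁻¹(p) + ln(1 + b/2)/s). With s = 0.7 and b = ±20%, the shifts are ln(1.1)/0.7 = 0.136 and ln(0.9)/0.7 = −0.151. For p = 5%: Φ(−1.645 + 0.136) = 6.6% and Φ(−1.645 − 0.151) = 3.6%.

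| Underlying success | Over-recorded (diet) | Under-recorded (control) | Difference, opposite biases | Difference, diet arm only |
|---|---|---|---|---|
| 5% | 6.6% | 3.6% | about 3 points | about 1.6 points |
| 10% | 12.6% | 7.6% | 5 points | 2.6 points |
| 20% | 24% | 16% | 8 points | 4 points |
| 40% | 45% | 34% | 11 points | about 5 points |

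At 5%, changing s from 0.5 to 1.0 moves the opposite-bias difference from 4.1 to 2.1 points.

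**Which row is most relevant.** The article assumes a 35-point difference and reports "alpha = 5% and power = 80%, we need 22 children for each group", without giving the control rate. The two-sided pooled formula is

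n = [1.96 √(2p̄(1−p̄)) + 0.842 √(p₁(1−p₁) + p₂(1−p₂))]² / 0.35²

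With 5% v 40%, p̄ = 0.225 and n = (1.157 + 0.451)²/0.1225 = 21.1, so 22. The same formula gives 25 at a 10% control rate and 31 at 30%; an unpooled variance gives 22 at 10%. The stated 22 is therefore compatible with a low control rate, so the top rows of the table are the closest to the trial's own planning.

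**False-positive rate.** These are exact enumerations of the uncorrected chi-square test, 22 per arm, b = 20% in size, s = 0.4 to 0.8:

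- Underlying 5%: 1.5% without bias; 2.2-3.6% with the diet arm only; 2.3-5.2% with opposite biases.
- Underlying 10%: 4.3%; 5.2-7.5%; 6.7-14.2%.
- Underlying 20%: 5.1%; 6.0-8.8%; 9.0-20.8%.

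**The two clocks.** Counting from the start of baseline, randomization is at week 2 and baseline ends at week 4. Six weeks after randomization is week 8; six weeks after baseline is week 10. The two descriptions of the usual-care visit differ by two weeks.

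**The case against.** Much of the case on the other side has force.

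- **Disclosure and baseline window are not spelled out.** The article says blinding is impossible; it does not say when the allocation is disclosed, nor that all four weeks form the reference count. A reader might infer that half of the denominator is certainly contaminated. The text does not establish that. It does fix randomization at mid-baseline with no safeguard described, and the four weeks are the only baseline defined, so the inference is reasonable.
- **Who keeps the calendar is not stated.** Stratification includes children in a residential centre, so families cannot be assumed to be the only recorders.
- **Direction is not given.** A reader might infer that the bias favours the diet, with cut-offs moving in opposite directions. That is only one assumed scenario; bias could also mask a benefit. A recording habit that persists into follow-up would largely cancel in the ratio.
- **Other mechanisms fit poorly.** Early dietary change is not suggested, since a dietician introduces the diet during the admission week. Withdrawal of disappointed controls is attrition, and later randomization would only postpone it.
- **It is repairable.** Because seizures are recorded by date, weeks 1-2 can be separated. A reader might infer that the baseline is beyond repair; that is true only of an analysis that keeps all four weeks.
- **Follow-up stays open-label** whatever week is chosen. This is true, but it is no reason to add a second, avoidable exposure.

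**Conclusion.** The point holds as a weakness in a stated design choice. The article places randomization midway through the baseline of an unblinded trial and describes nothing that protects the seizure count behind the primary outcome. Two links are inferred: that the allocation is known when it is made, and that all four weeks are the reference.

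The size of any bias cannot be derived from the document. Under the assumed 20% mis-recording it is about 1.6 to 3 points at a 5% underlying success rate, rising to 8 points at 20% if the arms err in opposite directions. On its own that would not produce the 35-point difference the trial is sized for, but it can raise the false-positive rate. The change is worth making because the exposure touches the primary outcome and is cheap to remove. The sample size of 22 per group is not affected.

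**What to change.** Randomize, or at least disclose the allocation, only after the four-week baseline calendar has been handed in and all T0 assessments are complete. No baseline time then follows known allocation, and mis-recording prompted by it can no longer move the baseline cut-off. The cost is up to two weeks less lead time for booking the admission.

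If admission planning needs the earlier allocation, define the primary baseline rate from the two pre-randomization weeks using the dated calendar, keep the four-week count as a sensitivity analysis, and complete T0 questionnaires before disclosure. The cost is a noisier two-week baseline in both arms.

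In either case, state the baseline window and the time of disclosure explicitly. Reconcile the start of the 6-week clock for usual care between Sample Size and the notes to Figure 2 and Table 1.

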**Figure 2 F2:**
[figure not shown]
**Timeline of the study**. Note: T0 = baseline; T1 = Admission; T2 = 6 weeks after baseline period; T3 = 4 months after baseline period; FU1 = 3 months follow-up; FU2 = 6 months follow-up; FU3 = 9 months follow-up; FU12 = 12 months follow-up.

**Table 1 T1:** Overview of measurements per time point

Measurement	T0	T1*	T2	T3	FU1*	FU2*	FU3*	FU4*
Demographic characteristics	x							

Clinical measurement	x	x	x	x	x	x	x	x

National Hospital Seizure severity scale	x	x	x	x	x	x	x	x

Side effects of Anti-Epileptic Drug	x	x	x	x	x	x	x	x

Credibility And Expectancy Questionnaire	x							

Peabody Picture Vocabulary test	x			x				x

Beery Developmental Visual-Motor Integration test	x			x				x

Fepsy computerized test	x			x				x

Kaufman Assessment Battery	x			x				x

Actigraphy	x			x				x

SEV Questionnaire	x			x				x

SDQ Questionnaire	x			x				x

POMS Questionnaire	x			x				x

The Personal Adjustment and Role Skills Scale	x			x				x

The Hague Restrictions in Childhood Epilepsy Scales	x			x				x

EuroQol	x			x				x

TAPQOL or TACQOL	x			x				x

Blood	x		x	x	x	x	x	x

Urine	x		x	x	x	x	x	x

Keton bodies measurement	x	x	x	x	x	x	x	x

ECG	x			x	x	x	x	x

T0 = baseline; T1 = Admission; T2 = 6 weeks after baseline period; T3 = 4 months after baseline period; FU1 = 3 months follow-up; FU2 = 6 months follow-up; FU3 = 9 months follow-up; FU12 = 12 months follow-up; *= intervention group only.

Patients in the usual care group will visit the multidisciplinary team (nurse practitioner, paediatrician and neurologist) at time points T0, T2, and T3 and will have a neurocognitive assessment at T0 and T3. In case of drop-out, a visit with the multidisciplinary team and a neurocognitive assessment will take place.

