#### Secondary outcome

##### Seizure severity

The National Hospital Seizure severity scale (NHS3) [26] is a structured interview in which the clinician rater assigns a score to seizure severity based on interference with patient function. Information is gathered from the patient and witnesses, if available. Eight questions are asked about: tonic-clonic movements, falling, injury, incontinence, altered consciousness, postictal impairment, and disruptive automatisms.

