##### Neurocognitive assessment

*Peabody Picture Vocabulary test*

The Peabody Picture Vocabulary test (PPVT-III-NL: Dutch version) is an individually administered measure of receptive vocabulary [27]. The test can be administered beginning at the age of 2 1/2 years. The child listens to the examiner's stimulus word and must choose the picture that best describes the word from a 4-picture multiple choice array. The score on this test can be interpreted as an achievement test of the child's vocabulary that does not require a verbal response and as a screening measure of verbal ability. There is supportive data for the validity of the PPVT-III as a measure for global cognitive intelligence.

*Beery Developmental Visual-Motor Integration test*

The Beery Developmental test of Visual-Motor Integration (Beery-VMI) is a widely used assessment of psychomotor development. It measures problems with visual perception, motor coordination, and visual motor integration. The 30-item test can be administered from the age of 2 years. The Beery VMI was standardized on a national US sample of 1,737 individuals age 2 to 18 years (2010) and 1,021 adults ages 19-100 (2006), and has proven reliability and validity [28].

*Fepsy computerized test*

The Fepsy is a neurocognitive computerized test battery consisting of different subtests. For this study we use the simple auditory and visual reaction times, in which the stimulus exposure endures until a push-button (space-bar) response is given [29]. Simple reaction tests give information on alertness functions and on the speed at which the information processing system is activated. We also use the binary choice reaction task in which a combination of accuracy and speed of responses are measured. This test measures the speed of central information processing. Finally, we use the finger tapping task in which motor activation and fluency is measured. In general, these tests can be administered from the age of 6.

*Kaufman Assessment Battery*

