The Kaufman Assessment Battery for Children II (K-ABC II) is used to investigate the level of information processing capacities of children beginning at the age of 2 1/2 years [30]. Two subtests will be administered: (1) Number recall, which is a measure of sequential processing and short term memory. The examiner says a series of numbers and the child repeats them. Digit span forward is considered a measure of efficiency of attention or "freedom from distractibility" and (2) conceptual thinking, which is a measure of nonverbal reasoning skills. The child looks at pictures and determines the one that does not belong.

*Actigraphy*

During the administration of the PPVT-III and the K-ABCII test, an actigraphic device (Actiwatch^® ^model AW4: Cambridge Neurotechnology Ltd., United Kingdom) will be used to assess motor activity as a measure of alertness. As some of the children in the design are not testable with the described cognitive tests we decided to use an assessment of motor activity in a standardized situation. A wrist watch will be used that translates activity into movement of the watch hand. Registration takes place in a standardized way during the first 10 minutes of the Peabody Picture Vocabulary test and the first 5 minutes of the K-ABC-II test. When patients are not eligible to perform the neurocognitive assessment, the wrist watch will be used for 15 minutes during the visit at the nurse practitioner's office while watching a DVD with songs and pictures.

*SEV Questionnaire*

The SEV questionnaire (Sociaal Emotionele Vragenlijst: Social Emotional Questionnaire) is a DSM-IV oriented questionnaire which is used to assess four domains of behavioral and social emotional dysfunction. These domains are: Attention Deficit Hyperactivity Disorders, Oppositional Defiant behavior and Conduct Disorders, Anxiety and Depression, and Autism spectrum disorders. The questionnaire consists of 72 items describing problem behavior [31].

*SDQ Questionnaire*

The Strengths and Difficulties Questionnaire (SDQ) is a brief behavioral screening questionnaire that provides balanced coverage of children and young people's behaviors, emotions, and relationships [32]. The SDQ is applicable to children beginning at the age of 4 and asks about 25 attributes that are divided into five relevant dimensions: namely conduct problems, emotional symptoms, hyperactivity, peer relationships, and pro-social behavior.

*POMS Questionnaire*

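### Blinding is declared impossible for researchers as a whole, although the neurocognitive examiner need not know the allocation at T3

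*Protocol article*

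**What the plan says.** The blinding statement is one sentence under Randomization and procedure: "In view of the nature of the treatments, blinding of the patients and researchers is not possible". It makes no exception, and no other section provides for a masked examiner, rater or calendar reader.

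Two of the neurocognitive instruments are described as given by an examiner. For the PPVT-III, "The child listens to the examiner's stimulus word and must choose the picture that best describes the word". For the number-recall subtest of the K-ABC II, "The examiner says a series of numbers and the child repeats them". In Timeline of the study, these assessments are scheduled separately from the visits to the multidisciplinary team. The diet group is tested at T0, T3 and FU4. The usual care group "will have a neurocognitive assessment at T0 and T3".

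On the primary outcome, the abstract says: "The primary outcome measure is the proportion of children with a 50% or more reduction in seizure frequency". The Seizure frequency section says "A seizure calendar is used to record seizures" and "Types of seizures are described and labelled in accordance with ILAE classification". It adds that number and type are entered on the day of the event. It does not say who keeps the calendar, who assigns the type, or who derives the responder status.

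**The concern.** In an open-label trial, the outcomes best protected are those assessed by someone who does not know the arm. Families cannot be masked to a diet, and neither can the dietician, nurse practitioner, paediatrician and neurologist who start and monitor it. A person who only gives and scores a vocabulary or memory test is in a different position, because nothing in that task depends on the arm.

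By treating all researchers alike, the sentence gives up this protection without a reason that applies to the examiner. Neurocognitive functioning is part of the stated effect question. Prompting, pacing, encouragement and the scoring of unclear responses can all be influenced by knowing who received the diet. The stake is the credibility of the T0-T3 difference between arms on examiner-administered tests.

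**Working it through.** The sentence is a statement about design and contains no figure to reproduce. The check is whether the reason given reaches each role that the article describes.

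1. **Families and children.** They prepare and eat the diet, or do not. The reason applies and masking is not possible.

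2. **Treating team.** Timeline of the study lists a nurse practitioner, dietician, paediatrician and neurologist for the diet group, and the same team without the dietician for usual care. They run the diet or see its monitoring. The reason applies.

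3. **Neurocognitive examiner.** The article uses this term for the PPVT-III and the K-ABC II. The assessment is scheduled separately from the team visits in both arms. Under Actigraphy, a child who cannot be tested has the recording made at the nurse practitioner's office instead, which suggests that testing normally takes place elsewhere. Nothing in the tests calls for the allocation. The reason does not apply.

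4. **Other neurocognitive and behavioural measures.** The Fepsy is computerized and actigraphy is a device reading, so examiner influence is smaller. Parent-rated scales such as the PARS-III, and the parent-rated side-effect list, share the families' lack of masking. The point does not extend to these.

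5. **Seizure severity.** The NHS3 "is a structured interview in which the clinician rater assigns a score to seizure severity based on interference with patient function", with information from the patient and witnesses. Masking that rater would be harder, because the people interviewed know the arm. This outcome is left outside the recommendation.

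6. **Seizure calendar.** Type and number are recorded as events occur. Deriving a count and a responder status from the entries can be done on data coded without arm. The entry itself is made by someone whose knowledge of the arm this does not change.

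**Where the controlled comparison lies.** Both arms are tested at T0 and T3, while FU4 is for the diet group only. T3 is therefore the assessment at which masking matters. Randomization takes place halfway through the 4-week baseline, and the text does not say whether T0 testing comes before or after it. If T0 testing can come after allocation, the same instruction is useful there.

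**The case against.** The strongest counter-argument is that a condensed article often leaves to the full protocol who tests, labels and counts, so unmasked assessment is inferred rather than stated. That stands for the calendar, where the article is silent. It is weaker for the general point, because the article does not merely omit masking of assessors: it says that blinding of researchers is not possible and gives a reason that does not reach the examiner.

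It can also be said that these are standardized tests, that some children cannot do them, and that a child or parent may reveal the diet. All of this is true. It limits the gain but does not remove it.

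A reader might go further and infer that the primary outcome is materially exposed through unmasked labelling and counting. The document does not support this. It does not say that calendars are on paper, kept by parents or labelled afterwards. Recording on the day of the event points away from a later labelling step. The article also does not say that seizure type decides whether an event counts towards the 50% reduction. Masked counting would leave the recorder's own bias untouched, and a separate calendar reader might be an added resource.

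A reader might also try to size the effect by moving one child. With 25 per arm and uncorrected Pearson chi-square:
- 8/25 versus 2/25: 50 × (8×23 − 2×17)² / (25×25×10×40) = 4.50, p = 0.034.
- 7/25 versus 2/25: 50 × (7×23 − 2×18)² / (25×25×9×41) = 3.39, p = 0.066.

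The arithmetic is right, but these counts sit near the threshold by choice. Their differences are 24 and 20 points, against the 35 points in the sample-size section. Nearer the planned difference, one child changes nothing: 10/25 versus 1/25 gives p = 0.002 and 9/25 versus 1/25 gives p = 0.005. Such examples show how sensitive a small trial is to a single classification. They do not measure labelling, counting or examiner bias.

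**Conclusion.** The point holds in a limited form. The nature of the diet justifies leaving families and the treating team unmasked, but does not justify the same for the neurocognitive examiner. The sentence therefore accepts an avoidable risk of assessor bias in the T0-T3 comparison of examiner-administered tests. This is a risk, not a demonstrated bias, and the document gives no basis for estimating its size.

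The conclusion assumes that the examiner is not a member of the treating team. The separate scheduling suggests this, but the article does not state it. For the primary outcome, the benefit of masked handling is at most partial. Priority: optional, or at most a weak recommendation.

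**What to change.** Limit the blinding sentence to children, families and the treating team, and add that:
- the existing neurocognitive examiner is not told the allocation at T3;
- families are asked before the session not to mention the diet;
- any unmasking of the examiner is recorded.

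Where existing staff allow, derive seizure counts and responder status from calendar data coded without arm, and acknowledge that whoever keeps the calendar remains unmasked.

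The cost is a briefing instruction, a note on the test form and, for the optional calendar step, coding of the data. Masking will be imperfect. Treatment, visits, measurements and sample size do not change, and the examiner step needs no extra staff if the examiner is indeed outside the treating team.
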